# Intratissue percutaneous electrolysis and deep dry needling compared to a standard physiotherapy protocol in the treatment of whiplash syndrome: study protocol for a randomized controlled trial

**DOI:** 10.3389/fresc.2025.1670603

**Published:** 2025-11-03

**Keywords:** percutaneous electrolysis, dry needling, whiplash, myofascial pain syndrome, myofascial trigger point, intrafibrillar blood flow and elasticity of muscle fibers

## Abstract

**Background:**

Whiplash syndrome is one of the most frequent consequences of traumatic pathology caused traffic accidents. The acceleration-deceleration mechanism of energy transmitted to the neck causes abnormal maneuvers in the area and muscle pain. The most common form of muscle pain in the neck and head is myofascial pain syndrome, caused by myofascial trigger points, these being clinically defined as painful, sensitive and hyperirritable nodules that are located on tense muscle bands. These painful nodules are treated with different physiotherapy techniques, there being no international consensus regarding their diagnosis and recommended interventions.

**Objective:**

The primary objective of this study is to evaluate the effectiveness of percutaneous intratissue electrolysis (EPI) on intrafibrillar blood flow and muscle fiber elasticity compared to deep dry needling (DN) and standard physiotherapy. Secondary objectives include the assessment of perceived pain, disability, and clinical outcomes at follow-up.

**Methods:**

This single-blind randomized clinical trial will be conducted in patients residing in Melilla with whiplash syndrome due to traffic accidents. Participants will receive interventions targeting the sternocleidomastoid and/or levator scapulae muscles. Assessments will be conducted at baseline, after four weeks of intervention, and at three months post-intervention to evaluate medium-term effects. Our hypothesis is that EPI will produce greater improvements in the study variables compared to DN and standard physiotherapy.

**Discussion:**

Percutaneous electrolysis has shown positive clinical effects in various musculoskeletal pathologies; however, its impact on intrafibrillar blood flow and muscle fiber elasticity remains unexplored. This study aims to provide reference clinical data on these physiological outcomes and compare the effects of invasive vs. standard physiotherapy interventions, supporting the development of evidence-based protocols for whiplash-associated disorders.

**Clinical Trial Registration:**

NCT06938425.

## Introduction

1

Whiplash syndrome (WAD) is a common soft tissue injury of the neck caused by forced flexion-extension movements, usually after traffic accidents (1–3).

WAD caused mainly by vehicle collisions, has an annual incidence in Western countries of between 200 and 300 cases per 100,000 inhabitants (4). It is the most frequent traumatic pathology in the forensic field, with a high incidence in Spain, with the Autonomous City of Melilla standing out (5–10). Clinical manifestations may not be immediate, and between 10%–42% of cases evolve into chronicity (2, 11). Around 16% are left with severe and persistent disability (12). Diagnosis is primarily clinical, as imaging tests are often inconclusive (13, 14). Likewise, the literature indicates that psychological, social, and contextual factors influence the transition to chronicity, underscoring the need for an early and interdisciplinary approach (15).

Myofascial pain is a frequent complication of WAD, associated with the presence of myofascial trigger points (MTrPs), responsible for cervical and cranial pain, with a prevalence that can reach 93% in some populations (16–21). Myofascial pain syndrome (MPS) is characterized by the presence of hyperirritable nodules in tight muscle bands that generate local or referred pain and muscle dysfunction (21, 22). Its pathophysiology involves abnormal stimulation of sensory nerves and excessive release of acetylcholine, resulting in persistent contractions and pain (23, 24). PGMs commonly appear in muscles such as the upper trapezius, sternocleidomastoid and levator scapulae, being frequent in SLC (25–34).

Diagnosis is based on clinical criteria such as spontaneous pain, presence of tight band, tender point and referred pain, and can be complemented with electromyography, ultrasonography, elastography and other techniques (35–45). In addition, factors such as hormonal, nutritional and postural deficiencies may perpetuate the dysfunction (46).

The treatment of WAD has evolved away from the use of drugs such as analgesics, anti-inflammatory drugs and muscle relaxants due to their adverse effects and limited efficacy (47, 48). Rest and the use of soft collars are discouraged because they delay recovery and promote complications such as muscle atrophy (47, 49, 50). Currently, early mobilization and supervised exercise are prioritized, although the efficacy of spinal manipulations is still controversial (49).

In the field of physical therapy, there is no single consensus protocol for treating MPS in the context of WAD, although the common goal is to restore muscle function and deactivate MTrPs (51–53). Individualized programs integrating manual therapy, myofascial release, dry needling (DN), therapeutic exercises, and electrotherapy have been shown to be effective (14, 54–56). International clinical guidelines recommend a multimodal approach based on a combination of active and passive techniques, along with self-care (57). A recent meta-analysis confirmed that combined techniques achieve better results in terms of pain reduction and sensitivity improvement (58). Still, more methodological quality is needed to establish a standardized protocol (47, 50, 59–61).

Dry needling (DN) is a technique increasingly used to treat musculoskeletal pain, especially in MTrPs, by inserting a needle without substance, provoking a mechanical stimulus to deactivate it (62–66). It is classified into superficial dry needling (SDN) and deep dry needling (DDN), the latter being the one that goes through the MTrPs and can induce a local spasm response (63, 65, 66). The most recognized techniques are those developed by Hong and Gunn, applied in pathologies of the neck, shoulder and back (67–73). Its indications are focused on the treatment of musculoskeletal pain, with absolute and relative contraindications such as belonephobia, coagulation disorders, pregnancy or immune diseases (74–91). If performed under conditions of asepsis, informed consent and ultrasound guidance, it is a safe technique, although adverse effects such as hematoma, infection or pneumothorax may occur (83, 92–110).

DN acts through the release of endogenous opioids, washout of inflammatory mediators, mechanical destruction of altered muscle fibers, and normalization of sarcomeric length (35, 111–118). The use of 0.30–0.32 mm stainless steel needles adapted to the treated region is recommended (98, 99). Studies suggest that DN can reduce pain and increase pressure threshold in the short term in cases of mechanical neck pain, although its long-term benefits compared with passive stretching are limited (89, 119–122). Some meta-analyses suggest that infiltrations may be more effective than DN in terms of pain reduction, with no significant difference in disability or mobility (123, 124). Currently, the evidence is insufficient to confirm their superiority over placebo (62, 93, 125–127).

Intratissue percutaneous electrolysis (EPI) is an invasive minimally physiotherapy technique that applies galvanic current through a needle to induce a controlled inflammatory response and promote tissue repair. By combining mechanical and electrical stimuli, EPI has demonstrated effectiveness in reducing pain and disability in tendinopathies and other musculoskeletal pain conditions, with favorable outcomes reported in the short, medium, and long term. Moreover, when adverse events are reported, they are generally infrequent and mild, although safety reporting remains limited and should be further standardized in future clinical trials (128–130). Designed by Sánchez Ibáñez in 2003, its application requires rigorous asepsis and ultrasound guidance to ensure safety and accuracy (98, 99, 101, 131).

Galvanic current is administered by means of an active cathode (needle) and an anode, with doses determined by Faraday's Law: high intensities and short times for regeneration; low intensities and long times for analgesia (99). It is contraindicated in cases such as unstable epilepsy, open wounds or metallic implants (83). EPI has shown pain reduction and functional improvement with moderate evidence, especially in chronic tendinopathies combined with eccentric exercise (99, 132, 133). However, some studies have found no relevant differences with respect to placebo or DN (134–137). It has also been evaluated in conditions such as lateral epicondylalgia, temporomandibular dysfunctions and rotator cuff pain, where it has outperformed DN in some cases (130, 133, 138–140), although more research is needed to validate these results due to methodological variability (85, 130, 133, 141–147).

The primary objective of this research is to evaluate the efficacy of two physiotherapeutic interventions - percutaneous intratissue electrolysis (PIE) and deep dry needling (DDN) - in adults with WAD after traffic accidents and to see if there is an improvement in intrafibrillar blood flow and muscle fiber elasticity compared to a standard physiotherapy protocol. Secondary objectives include the evaluation and analysis of perceived pain, disability, and long-term variable clinical outcomes.

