### Study sample

2.2

The subjects will be recruited from a health center adhered to the agreement on health care derived from traffic accidents [Unión Española de Entidades Aseguradoras y Reaseguradoras (UNESPA) agreement] belonging to the Autonomous City of Melilla. The following inclusion and exclusion criteria will be used to select the sample.

The inclusion criteria for this study will be as follows:
-The study includes adults with whiplash syndrome (CIE-10- code S13.4) with pain in the cervical area after a traffic accident. Subjects will have to be treated in hospitals or private centers and referred to rehabilitation.-Patients must reside or stay in the Autonomous Community of Melilla during the intervention phase.-Subjects will have the presence of neck pain after suffering a traffic accident and the presence of at least one active trigger point in the sternocleidomastoid and/or levator scapulae muscles.-All subjects suffering a traffic accident and having a score of 5 or higher on the numerical scale (EN) of pain assessment.It will be a reason for exclusion:
-Patients doing anticoagulant treatment.-Patients who have suffered previous cervical trauma or who have undergone surgery in the last year.-Subjects who present any type of alteration (skin or infection, sensitivity or pain perception).-Subjects with central or peripheral nervous system affectation.-Patients who have problems with the material: allergy to metal, belonephobia (fear of needles).-Pregnant women.

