### Sample size

2.3

To date, there are no studies reporting on the use of deep dry needling and/or percutaneous intratissue electrolysis in patients who have suffered from whiplash syndrome, so that this randomized, blinded clinical trial will provide evidence for the effect size.

To calculate the population size, we used data published by the Directorate General of Traffic (DGT), updated in 2020, which identified 242 patients who were victims of traffic accidents in the city of Melilla. The Al-Therapy Statistics tool will be used for the sample calculation (https://www.ai-therapy.com/psychology-statistics/sample-size-calculator). Therefore, we will use a sample size of (*n* = 36) with a proportional distribution for each study group (GE1 group = 12 + GE2 group = 12 + Control group = 12) with an expected loss ratio (R = 15%) and a confidence interval (CI = 95%), this information is expanded in the Supplementary Material.

However, this calculation does not provide sufficient statistical power. A more robust estimation can be derived from validated clinical parameters reported in the literature: a minimum clinically important difference (MCID) of 2 points on the Numeric Rating Scale (NRS) for pain (151–153), a standard deviation of approximately 2.5 (154), and a pre–post correlation ranging between 0.5 and 0.7 (155, 156). Based on these assumptions, the required sample size would range from 20 to 31 participants per group (60–93 in total) to ensure adequate power.

Since the present study will include only 36 participants, it should be explicitly characterized as a pilot randomized controlled trial, designed to assess feasibility, refine procedures, and provide preliminary effect size estimates to guide the design of a fully powered clinical trial.

For the development of this research, a non-probabilistic intentional sampling will be used for the convenience of the study, due to the characteristics of the subjects to be studied. Strategies to ensure adequate inclusion of participants who meet the target sample size include collaboration with a health center affiliated with the UNESPA agreement on healthcare resulting from traffic accidents, rehabilitation physicians, and physiotherapy teams.

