### Randomization

2.4

Before patient inclusion, the research team will generate the allocation sequence and randomly assign patients consecutively to GE1, GE2, and the CG. A computerized random number generator will be used. Each participant will be treated separately to prevent any exchange of study information. The nature of the intervention in both groups does not allow blinding of patients and physiotherapists. It is therefore a single-blind study, where the evaluator does not know the nature of the intervention. The evaluator was unaware of the study objectives and the randomized distribution of patients to study groups, and he did not have access to the randomization sequence.

Before patient inclusion, the research team will generate the allocation sequence and randomly assign patients consecutively to GE1, GE2, and the CG. A computerized random number generator will be used. Each participant will be treated separately to prevent any exchange of study information. The nature of the intervention in both groups does not allow blinding of patients and physiotherapists. It is therefore a single-blind study, where the evaluator does not know the nature of the intervention. The evaluator was unaware of the study objectives and the randomized distribution of patients to study groups, and did not have access to the randomization sequence. The evaluator was blinded to treatment allocation throughout the study. Participants were explicitly instructed not to disclose their assigned intervention to the evaluator; treatments and assessments were performed by different staff in separate locations; and any potential unblinding events were systematically logged. At the end of follow-up, the evaluator recorded, for each participant, their guess of allocation (active/sham/don't know), allowing for a quantitative evaluation of blinding success.

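### Metallic implants, which the protocol itself names as a contraindication to EPI's galvanic current, are missing from the section 2.2 exclusions

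*Protocol article*

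**What the plan says.** The Introduction, in its account of how galvanic current is delivered through the EPI needle, states: "It is contraindicated in cases such as unstable epilepsy, open wounds or metallic implants". It does not qualify the implant by site, type or age.

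Section 2.2 (Study sample) opens its list with "The following inclusion and exclusion criteria will be used to select the sample". Two of its exclusions come near to implants:
- "Patients who have suffered previous cervical trauma or who have undergone surgery in the last year";
- "Patients who have problems with the material: allergy to metal, belonephobia (fear of needles".

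The other exclusions concern anticoagulants, skin, infection or sensory alterations, nervous-system involvement, and pregnancy. Implants appear nowhere in the list.

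Section 2.3 sets the group sizes: "GE1 group = 12 + GE2 group = 12 + Control group = 12". By Table 1 in section 2.5, GE1 is the EPI arm. The same section gives every EPI patient galvanic current through a needle in the sternocleidomastoid and/or levator scapulae.

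**The concern.** A randomised trial should admit only patients who could safely receive any of its arms, because chance decides which one they get. Here the document names a condition under which one arm's treatment should not be given, then prints an eligibility list that does not exclude it. A site that follows section 2.2 to the letter could randomise a patient with a metallic implant.

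What is at stake is the safety of that patient. If the implant is found only after allocation, the team must either give a treatment that its own protocol advises against or depart from the allocated treatment. A check before randomisation avoids both.

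**Working it through.** **Step 1. Match each EPI contraindication in the Introduction to the section 2.2 exclusions.**

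| Named in the Introduction | Nearest item in section 2.2 | Covered? |
|---|---|---|
| Unstable epilepsy | Nervous-system involvement | Plausibly |
| Open wounds | Skin alteration or infection | Plausibly |
| Metallic implants | Metal allergy; previous cervical trauma; surgery in the last year | Only in part |

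**Step 2. Test the partial cover for implants.**
- Metal allergy is a different condition. A patient can carry an implant without being allergic to metal.
- The surgery item reaches back one year, so it catches only recently placed implants.
- The trauma item catches hardware from an earlier neck injury. The sentence can be read with the one-year limit on surgery alone or on trauma as well. On the second reading, hardware from older neck trauma is also admitted.
- On either reading, a patient whose implant is more than a year old and who has had no previous cervical trauma passes the list, provided the other criteria are met.

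**Step 3. Chance of assignment to EPI.**
- Inputs (section 2.3): 12 in GE1, 12 in GE2, 12 in the control group. The total is 12 + 12 + 12 = 36, which reproduces the stated sample size.
- P(assigned to EPI) = 12/36 = 1/3.
- Section 2.5 describes random assignment to the three groups with no restriction for implants, so the same 1/3 applies to such a patient.

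**Step 4. If several such patients enrol.** The article gives no frequency of implants, so the number k is an assumption, shown only for scale. With fixed groups of 12, P(at least one assigned to EPI) = 1 − C(36 − k, 12)/C(36, 12).
- k = 1: 1 − 24/36 = 33%
- k = 2: 1 − (24 × 23)/(36 × 35) = 1 − 552/1260 = 56%
- k = 3: 1 − (24 × 23 × 22)/(36 × 35 × 34) = 1 − 12144/42840 = 72%

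If k = 0, the chance is zero. With the exclusion in place and applied before randomisation, it is zero for every relevant implant.

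**The case against.** The strongest reply is that the contraindication is background. It stands in the Introduction, gives examples rather than a closed list, and does not say whether an implant far from the neck matters when the needle is in a neck muscle. This stands as a limit on scope: the documents do not settle which implants count, and a clinician must. It does not remove the gap, because section 2.2 excludes no implant at all, not even one near the treated muscle.

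A second reply is that assignment is not treatment. Section 2.5 has patients evaluated before treatment, using clinical parameters and medical records. Section 2.6 includes a history interview. EPI is ultrasound-guided and given by therapists with more than ten years' experience in invasive techniques. This also stands, so 1/3 is the chance of assignment and not of exposure to current. None of these steps is said to look for implants.

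A third reply is that a journal article condenses the full protocol. That does not help here: section 2.2 prints the selection criteria and does not refer eligibility elsewhere.

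A reader might infer three further points that the documents do not support.
- *Allocation precedes screening.* Section 2.4 says "Before patient inclusion, the research team will generate the allocation sequence and randomly assign patients consecutively to GE1, GE2, and the CG". The opening phrase fits ordinary advance generation of the sequence, and section 2.2 says the criteria select the sample. No order error can be read from this.
- *The planned current measures the harm.* The dose in section 2.5 is the ordinary EPI dose, and nothing in the article links it to injury in a patient with an implant.
- *Coagulation disorders and immune disease are the same kind of omission.* For dry needling the Introduction speaks of technique use "with absolute and relative contraindications such as belonephobia, coagulation disorders, pregnancy or immune diseases". It does not say which are absolute, and a relative contraindication need not be an exclusion. No contradiction with section 2.2 follows.

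**Conclusion.** The point holds, as a safety gap in the eligibility rule that should be fixed. Of the three contraindications to galvanic current named in the Introduction, two are plausibly covered by section 2.2. Metallic implants are covered only where surgery in the last year or previous cervical trauma happens to exclude the patient. An otherwise eligible patient with an older implant and no previous cervical trauma has a 1/3 chance of being assigned to EPI.

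This rests on two assumptions: that the Introduction's statement is meant to apply to the EPI given in this trial, and that the implant is one the clinical lead would regard as relevant. The number of such patients among 36 is unknown and may be zero.

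It would go too far to conclude that a third of patients with implants will receive the current, since safeguards that are informal but real stand between assignment and treatment. Nor is any bias in the estimates or tests shown.

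**What to change.** Add metallic implants to the exclusions in section 2.2, with the clinical lead stating which sites or types count for current applied in the neck. Ask every candidate about them before randomisation, in the same way whichever arm may follow, so that all three arms come from the same eligible population.

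The cost is one line in the criteria, one clinical decision and one screening question. A few candidates may become ineligible and have to be replaced to reach 36. How many cannot be estimated from the article.

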## Methods

2

### Study design

2.1

This research will be conducted as a single-blind randomized clinical trial in patients residing in the Autonomous City of Melilla with whiplash syndrome following a traffic accident. This research uses the Standards for Quality Improvement and Reporting Excellence (SQUIRE) guidelines (148) and will be conducted according to the Consolidated Standards for Reporting of Clinical Trials (CONSORT) criteria (149). The Standard Protocol for Interventional Trials (SPIRIT) Item Recommendations checklist has been added as Supplementary Material (150). A flow chart of the study design is shown in Figure 1.

**Figure 1 F1:**
[figure not shown]
Flow chart of the study design.

### Study sample

2.2

The subjects will be recruited from a health center adhered to the agreement on health care derived from traffic accidents [Unión Española de Entidades Aseguradoras y Reaseguradoras (UNESPA) agreement] belonging to the Autonomous City of Melilla. The following inclusion and exclusion criteria will be used to select the sample.

The inclusion criteria for this study will be as follows:
-The study includes adults with whiplash syndrome (CIE-10- code S13.4) with pain in the cervical area after a traffic accident. Subjects will have to be treated in hospitals or private centers and referred to rehabilitation.-Patients must reside or stay in the Autonomous Community of Melilla during the intervention phase.-Subjects will have the presence of neck pain after suffering a traffic accident and the presence of at least one active trigger point in the sternocleidomastoid and/or levator scapulae muscles.-All subjects suffering a traffic accident and having a score of 5 or higher on the numerical scale (EN) of pain assessment.It will be a reason for exclusion:
-Patients doing anticoagulant treatment.-Patients who have suffered previous cervical trauma or who have undergone surgery in the last year.-Subjects who present any type of alteration (skin or infection, sensitivity or pain perception).-Subjects with central or peripheral nervous system affectation.-Patients who have problems with the material: allergy to metal, belonephobia (fear of needles).-Pregnant women.

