### Intervention

2.5

Study subjects are randomly assigned to one of the following three groups: Experimental Group 1 (EG1), Experimental Group 2 (EG2) or the Control Group (CG) through a computer randomization system using the statistical program Epidat V4.2.

Once the subjects have been informed of the entire study procedure and have signed the informed consent form (Annexes I, II) this information is expanded in the Supplementary Material, they will be evaluated before starting treatment. Subjects will receive an initial evaluation based on clinical parameters and follow-up medical records. The data will be collected by an evaluator and integrated into our research databases using an Excel spreadsheet.

Both experimental groups will receive an invasive physiotherapy protocol (one weekly session) applied to the sternocleidomastoid and/or levator scapulae muscles, in addition to the standard physiotherapy program. The intervention will be conducted over four weeks, with a total of 20 sessions (five per week), following rehabilitation medicine guidelines for this condition. This standardization ensures consistency in treatment exposure and enhances reproducibility of the protocol.

The therapeutic exercise program will be delivered under the supervision of trained physiotherapists. Exercises will be performed in progressive phases, with adjustments in intensity, resistance, and volume according to predefined progression criteria. Details of the exercise program are summarized in Table 1.

**Table 1 T1:** Relationship between standard physiotherapy procedure and intervention.

Intervention procedure	Physiotherapy intervention	Description	Duration/Repetitions	Frequency	Subjects
Experimental group	EPI	Hong technique on localized MTrPs (ECOM and/or Levator scapulae)	1× week	1 day for 4 weeks	GE_1_
	Dry needling	Hong technique on localized MTrPs (ECOM and/or Levator scapulae)	1× week	1 day for 4 weeks	GE_2_
Standard physiotherapy procedure (GE + GC)	Thermotherapy + analgesic electrotherapy	Microwave or thermotherapy techniques combined with TENS.	15 min	5 days for 4 weeks	GE + GC
	Massage therapy	Friction maneuvers, kneading, and manual stretching of the muscle and affected area.	20 min	5 days for 4 weeks	GE + GC
	Manual therapy	- Deep friction massage - Contraction- relaxation technique passive - Stretching and self-stretching	10 min	5 days for 4 weeks	GE + GC
			2–3 repetitions		

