### Data collection procedure, monitoring, and management

2.7

During data collection, the information will be anonymized, and all data from the clinical history, anamnesis, and the various study variables will be compiled. Once all the information has been gathered, an individual palpatory assessment of the sternocleidomastoid and/or levator scapulae muscles will be performed, along with a set of tools and instruments for measuring variables.

The procedure for taking variable measurements and evaluations will be carried out before the start of the program (Pre-Test), four weeks after the completion of the intervention (Post-Test).

Both the initial assessment (Pre-Test) and the four-week measurements (Post-Test) will be performed by an evaluator unaware of the nature of the intervention, at a designated location, with easy access for the patient and prior appointment confirmation.

The data will be added to the database created for this purpose and managed by the principal investigator. A data collection notebook will be used as supporting material and will be used for statistical analysis.

The results of the research will be presented as a summary of the outcome measures, along with the estimated effect size and its precision. Statistical analysis will be performed according to the intention-to-treat principle using SPSS software, with statistical significance set at *p* < 0.05. Descriptive statistical analysis of the different variables will be performed. Results will be evaluated by comparing differences between groups using linear mixed model statistics and the *t*-test to test the hypothesis that group means are or are not significantly different from each other.

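### The location criterion covers only the four treatment weeks, so temporary visitors can be randomised who may be unavailable for the three-month assessment

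*Protocol article*

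**What the plan says.** Section 2.2 (Study sample) holds the only location criterion: "Patients must reside or stay in the Autonomous Community of Melilla during the intervention phase". Section 2.5 (Intervention) fixes the length of that phase: "The intervention will be conducted over four weeks, with a total of 20 sessions (five per week").

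The population is described more narrowly elsewhere. Section 2.1 places the trial "in patients residing in the Autonomous City of Melilla with whiplash syndrome following a traffic accident", and the Abstract likewise speaks of residents.

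The assessment schedule appears twice. The Abstract states: "Assessments will be conducted at baseline, after four weeks of intervention, and at three months post-intervention to evaluate medium-term effects". Section 2.7 puts measurement "before the start of the program (Pre-Test), four weeks after the completion of the intervention (Post-Test") and lists no three-month visit. The next paragraph of Section 2.7 refers to the same post-test as a measurement at four weeks, and places the assessments "at a designated location, with easy access for the patient and prior appointment confirmation".

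**The concern.** An eligibility rule about location serves two purposes: the patient can be treated, and the patient can be measured. This one secures only the first. Someone injured while visiting Melilla, who stays for the four treatment weeks and then goes home, meets the criterion and may have no value at the last assessment.

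Most of the instruments need the patient present. Doppler ultrasound and elastography (Section 2.6.1) and pressure algometry (Section 2.6.2) cannot be done at a distance. The numerical pain scale and the disability questionnaire could be, but the article describes no remote collection.

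The outcomes at stake are chiefly those behind the follow-up objective, which the Abstract lists among the secondary objectives. With 12 patients per arm, each missing patient is a visible fraction of the comparison, and a measurement not taken cannot be recovered by analysing according to intention to treat. The two descriptions of the population also leave a recruiter unable to tell whether a visitor is eligible.

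**Working it through.** **Step 1: the eligibility window against the assessments.** Count weeks from the start of treatment. The intervention lasts 4 weeks (Section 2.5), so the location requirement ends at about week 4.

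| Assessment | Source | Approximate week | Inside the window? |
|---|---|---|---|
| After four weeks of intervention | Abstract | 4 | At its edge |
| Three months post-intervention | Abstract | 4 + 13 = 17 | No |
| Post-test, read as four weeks after completion | Section 2.7 | 4 + 4 = 8 | No |
| Post-test, read as the four-week measurement | Section 2.7, next paragraph | 4 | At its edge |

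The three-month visit lies outside the window however Section 2.7 is read. The post-test lies outside it on one of two readings. If that reading is the intended one, and Section 2.7's list of visits is complete, a visitor who leaves after treatment has no post-treatment value at all.

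**Step 2: the plan's own loss allowance.** Section 2.3 gives N = 36, 12 per arm, with 15% expected loss. 0.15 × 36 = 5.4 patients, or 5.4 / 3 = 1.8 per arm. The allowance is not tied to any cause of loss.

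**Step 3: what visitors could add.** The article gives no visitor share, so 10–20% is purely an assumption. One departing visitor is 1/12 = 8.3% of an arm at that visit. A 10% share is 0.10 × 36 = 3.6 patients; 20% is 0.20 × 36 = 7.2.

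- Allowance covers none of them and all leave: 5.4 + 3.6 = 9.0 (25%) at a 10% share; 5.4 + 7.2 = 12.6 (35%) at a 20% share.
- Allowance already covers those who leave: total loss stays at 5.4 (15%). At a 10% share this is possible even if all leave, since 3.6 < 5.4. At a 20% share it requires that no more than 5.4 of the 7.2 leave; if all leave, the loss is at least 7.2 (20%).

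The range is therefore 15% to about 35%.

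**Step 4: what that range means for precision (illustration).** Section 2.3 supplies a 2-point difference on the pain scale, an SD of 2.5 and a pre–post correlation r of 0.5 to 0.7. For change scores, SD = 2.5 × √(2(1 − r)). A two-sample t-test at two-sided 0.05 with 80% power (the power is assumed, as the article does not state it) needs 26 per group at r = 0.5 and 16 at r = 0.7. Dividing by 0.85 gives 31 and 19, close to the article's 31 and 20. On the same basis, pairwise power is:

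| Loss | Evaluable per arm | r = 0.5 | r = 0.7 |
|---|---|---|---|
| 15% | 10.2 | 40% | 60% |
| 25% | 9.0 | 36% | 54% |
| 35% | 7.8 | 31% | 47% |

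This treats patients with a missing visit as absent from that comparison. It concerns pain, a secondary outcome; the article gives no comparable figures for the two primary outcomes.

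**The case against.** The best reply is that little of this need happen. On the Abstract's schedule the first post-treatment assessment falls when the criterion still holds the patient in Melilla, and Section 2.7's second description of the post-test agrees. Only the three-month visit is then exposed, and it serves a secondary objective. A patient with baseline and four-week data also stays in the planned linear mixed model when the three-month value is missing. The trial is labelled a pilot and concedes inadequate power. A commitment to attend follow-up may be in the information and consent forms (Annexes I and II), which are not shown.

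Much of this stands, and it rules out three stronger readings that a reader might infer:

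- That visitors will have left before the outcomes are measured. The criterion permits this; the documents do not show that it will happen, nor that the post-test is affected.
- That total loss will be 25–35%. That needs an unsupported visitor share, every visitor leaving, and no overlap with the 15% allowance.
- That the loss will be informative because recovered patients are freer to leave. This is plausible, but nothing in the text shows it, and the criterion applies to all arms before randomisation.

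The reply does not remove the mismatch. The stated rule ends before the last stated assessment, and the text shown nowhere requires availability beyond it. The mixed model uses earlier data but does not supply the missing measurement. A pilot meant to assess feasibility and give preliminary effect sizes is not helped by avoidable attrition.

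**Conclusion.** The point holds as a mismatch between a stated eligibility rule and the stated assessments. Visitors are eligible under Section 2.2 but not under the population described in the Abstract and Section 2.1, and their required presence ends about three months before the last assessment in the Abstract. Whether the post-test is exposed as well depends on a conflict within Section 2.7 that must be reconciled.

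The size is not known from the documents. Per patient it is 8.3% of an arm at the visit missed. In total it lies between no excess over the planned 15% and about 35%, under an assumed 10–20% visitor share; the upper end further assumes that all visitors leave and that the allowance covers none of them. Bias from the loss is possible but not demonstrated. Confidence is high in the mismatch and low in any particular amount of loss. This is a cheap improvement rather than a flaw that undermines the trial.

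**What to change.** Reword the criterion in Section 2.2 to require residence in Melilla, or confirmed availability to attend in person there, through the last scheduled assessment. Check this before randomisation. Use the same population wording in the Abstract and in Sections 2.1 and 2.2. Reconcile the schedules in the Abstract and Section 2.7 so that the last scheduled assessment is unambiguous.

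The change is one line of eligibility wording plus the alignment, and it leaves the sample size and analysis as they are. Its cost is recruitment: some temporary visitors are excluded from a small single-centre pool. On the assumed 10–20% share, up to 3.6 to 7.2 of 36 places would have to be filled by others, fewer if some visitors can confirm that they will attend. If visitors are rare, both the cost and the benefit are small.
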